### Ethics

A rigorous anonymization process was applied to ensure compliance with privacy regulations (e.g., General Data Protection Regulation in the United States, Health Insurance Portability and Accountability Act in Europe and other applicable local laws) and to minimize the risk of patient reidentification. The anonymization strategy was developed following a reidentification risk assessment by Privacy Analytics an IQVIA company (Ontario, Canada) and was based on established privacy standards and expert methodologies [13]. 

### Study design and patient selection

This study will emulate a predefined clinical trial using the target trial emulation framework. In this framework, a RCT is simulated by systematically analyzing observational data using design and principles of RCT as template [12]. This framework includes eligibility criteria, treatment strategies, treatment assignment, study initiation and follow-up, outcomes, causal effect estimands and statistical analysis [15]. The protocol for this target trial is detailed in Table 1. A comparison with the details from the protocol from CONVINCE trial can be found at Supplemental Table 1.

**Table 1 Tab1:** Detailed study protocol for target trial emulation

Protocol component	Description of target trial	Description of emulation
	**Eligibility criteria**	
Inclusion criteria	1. Patients of ≥ 18 years old, with kidney failure 2. Initiate with high-flux HD or HDF in a European country where both HD and HDF can be offered. 3. Initiate within a time frame where at least 6 months of follow-up would theoretically be possible, with a maximum of five years 4. At baseline, there is the intention to follow a thrice-weekly schedule	1. Patients of ≥ 18 years old, with kidney failure 2. Initiate with high-flux HD or HDF between 1 January 2018 and 30 June 2024 in a European country where both modalities are represented in the available data 3. Patients prescribed a thrice-weekly schedule at the start
Exclusion criteria	1. Initiating with hemodialysis or hemodiafiltration at home	1. Initiating with hemodialysis or hemodiafiltration at home. 2. No data available within 14 days after dialysis initiation*
	**Treatment strategies**	
	1. Initiate HDF within the first 90 days after dialysis initiation (grace period) and continue HDF throughout the grace period receiving at least three HDF treatments every two weeks. 2. Initiate HD within the first 90 days after dialysis initiation (grace period) and continue HD throughout the grace period receiving more than three HD treatments every two weeks.	Same as target trial
	**Assignment procedures**	
	• Randomization between HDF and high-flux HD	• Randomization is emulated by cloning each individual and then assigning each clone to one of the treatment strategies
	**Follow-up**	
	• Starts at the randomization (assignment of a strategy, just before dialysis initiation) • Ends at death, informative censoring due to a competing event (kidney transplantation, recovery of kidney function, withdrawal from dialysis), administrative censoring (end of study or after 5 years) or loss-to-follow-up, whichever came first.	• Starts at the emulated randomization (assignment of a strategy, just before dialysis initiation, or within 14 days after initiation*) • Ends at death, informative censoring due to a competing event (kidney transplantation, recovery of kidney function, withdrawal from dialysis), administrative censoring (31 December 2024 or after maximum follow-up^♠^) or loss-to-follow-up, whichever came first.
	**Outcomes**	
Primary outcome	All-cause mortality	Same as target trial
Secondary outcome	• cause-specific mortality	Same as target trial • cause specific events are identified from relevant ICD-10 codes
Other outcomes	• all-cause hospitalizations • cause-specific hospitalizations • Cumulative length of hospital stay • dose–response relationship between convection volume and all outcomes above, in patients receiving HDF	Same as target trial • cause specific events are identified from relevant ICD-10 codes
	**Estimands**	
	• Intention-to-treat effect • 5-year survival using a cumulative incidence curve • Restricted mean survival time • Hazard ratio (HR) for the outcome, presented per year for a total of five years	Per protocol-effect • 5-year♠ survival using a cumulative incidence curve • Restricted mean survival time • Hazard ratio (HR) for the outcome, presented per year for a total of five years
	**Analysis plan**	
	• Intention-to-treat analysis, see Follow-up for censoring.	• Per protocol effect, see Follow-up for censoring. • Analysis is conducted in expanded data set that includes two clones for each eligible patient (one for each treatment strategy). IPCW is performed, both for informative and artificial censoring within the grace period, and for informative censoring after the grace period.

*Although this may theoretically lead to some level of immortal time bias, excluding everyone who does not have any data at day one of dialysis initiation will lead to selection bias (due to missingness). As the database for this study contains treatment related data in an outpatient setting, hospitalization at the start could be the reason for missing data in the first period

♠ To protect patient privacy, only the calendar quarter of dialysis initiation is available. We will therefore assign the midpoint of the quarter as the initiation date, as this approach minimizes misclassification. As a result, the maximum follow-up period will be 4 years and 9 months

HDF, hemodiafiltration; HD, hemodialysis; ICD-10, International Classification of Diseases; IPCW, inverse probability of censoring weighting

Inclusion criteria for this study will be:

Patients with age ≥ 18 years old at baseline;Patients with kidney failure who initiate dialysis and receive at least one high-flux HD or HDF treatment between 1 January 2018 and 30 June of 2024;Treatment occurs in a European country where both HDF and HD are available and where patients in the dataset receive both modalities each calendar year, ensuring representation of both treatments within each country;Patients prescribed thrice-weekly dialysis at the start.

Exclusion criteria will be:

Patients starting with dialysis at home;Patients who do not have the first treatment-related data available within 14 days after dialysis initiation.*.

*Because this database captures outpatient treatment only, data at treatment initiation may be missing for patients who were at another dialysis provider or who were hospitalized at that time. Excluding these patients could therefore introduce selection bias. Including patients with available data within the first 14 days may introduce a degree of immortal time bias; however, we believe for 14 days this will be limited. We will perform subgroup analyses of patients who have first treatment data at dialysis initiation compared to patients of whom first data is available within 14 days but not at the first initiation.

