**Fig. 1 Fig1:**
[figure not shown]
Weighting approach for Clone-Censor Weighting (CCW) and Marginal Structural Model (MSM). For the Clone-Censor-Weighting approach, weighting will take place every two weeks in the grace period of 90 days. Separate weights for artificial censoring for the treatment strategy, and for the informative censoring are calculated. Afterwards, weighting is repeated at the end of each year during the total follow-up of 5 years. For the Marginal Structural Model approach, weighting will take place every 6 months for the total follow-up of 5 years. Separate weights for treatment modality switches (IPTW) and for informative censoring are calculated. IPTW, inverse probability of treatment weighting; IPCW, inverse probability of censor weighting; Kt/V, metric for dialysis adequacy based on urea clearance (K), treatment time (t) and distribution volume (V); HbA1c, hemoglobin A1c

At two-weekly intervals, we will determine whether clones are adherent to their assigned treatment strategies. Of note, an event only contributes to the arm in which the patient is still uncensored at the time of event. For the HDF initiation strategy, patients will be censored at 90 days if they have not initiated HDF, and vice versa for the HD strategy. Individuals who die within the grace period while having received only one modality will have their replicated observations contribute follow-up time and a death event to both treatment strategies. This approach reflects the assumption that these early deaths could have occurred under either treatment strategy, as no clear modality choice had yet been established. By attributing these early events to both arms, this design prevents immortal time bias. Examples of censoring for the treatment strategies are shown in Fig. 2.

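### The initiation date is known only to the quarter and set to its midpoint, yet follow-up, the 14-day rule, the two-week windows and the 90-day grace period all count from initiation

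*Protocol article*

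**What the plan says.** The second footnote to Table 1 (♠) states: "To protect patient privacy, only the calendar quarter of dialysis initiation is available". It continues: "We will therefore assign the midpoint of the quarter as the initiation date, as this approach minimizes misclassification", and then: "As a result, the maximum follow-up period will be 4 years and 9 months".

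These rules count from initiation:

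- **Start of follow-up** (Table 1, Follow-up, emulation column): "Starts at the emulated randomization (assignment of a strategy, just before dialysis initiation, or within 14 days after initiation".
- **Exclusion** (Study design and patient selection): "Patients who do not have the first treatment-related data available within 14 days after dialysis initiation".
- **Subgroup** (note to the exclusion criteria): "subgroup analyses of patients who have first treatment data at dialysis initiation compared to patients of whom first data is available within 14 days"; the second group lacks data on the day of initiation itself.
- **Grace period** (Treatment strategies): 90 days from initiation, with the chosen modality started and then kept up within it.
- **Adherence** (Statistical analysis, CCW approach): "At two-weekly intervals, we will determine whether clones are adherent to their assigned treatment strategies". Grace-period weights are updated on the same two-week grid.

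The marginal structural model (MSM) also starts follow-up at dialysis initiation, but updates treatment and weights every 6 months.

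**The concern.** A date known only to the quarter cannot by itself support rules that work in 14-day steps. The midpoint gives the smallest average date error, which is the only sense in which it limits misclassification. It does not tell the analyst whether a patient had data within 14 days of starting, or in which fortnight a switch to HDF took place.

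The Treatment strategies section treats alignment of eligibility, assignment and start of follow-up as the safeguard against immortal time, and the Discussion claims it as a strength. The protocol argues that 14 days of possible immortal time is tolerable, but does not discuss a date error that can be about three times as long. If the midpoint is day 0, patients are dropped or kept according to their position in the quarter. Part of the early risk period, including any deaths in it, then lies before time zero.

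**Working it through.** **The plan's own figure.** The footnote derives a maximum follow-up of 4 years 9 months (57 months) from the midpoint rule. Five years less half a quarter is 60 - 1.5 = 58.5 months; five years less a full quarter is 60 - 3 = 57 months. The stated figure therefore matches a full-quarter deduction. Nor does the calendar force a cut: from mid-February 2018 to 31 December 2024 is 6.87 years. The midpoint rule does not yield 57 months, and 57 months does not cover the five yearly hazard ratios.

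**Inputs.** From the protocol: quarter-level initiation, midpoint assignment, a 14-day rule, 14-day windows and a 90-day grace period. Assumed, because the documents give no distribution: true starts uniform over a 91-day quarter, exact session dates, and the midpoint as day 0. Let e = true start minus midpoint, uniform on -45.5 to +45.5 days.

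**Date error.** Mean absolute error = 91/4 = 22.75 days; maximum 45.5 days.

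**The 14-day rule, for a patient treated from the true first day:**

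| First data relative to assigned day 0 | Formula | Share |
|---|---|---|
| Before day 0 | 45.5/91 | 50% |
| Days 0 to 14 | 14/91 | 15.4% |
| After day 14 | (45.5 - 14)/91 | 34.6% |

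The last row is wrongly excluded. It is 34.4% for a 90-day quarter, (45 - 14)/90, and 34.8% for a 92-day quarter, (46 - 14)/92. If first data truly come at day 14, wrongful exclusion rises to 45.5/91 = 50%. All this accepts data before day 0 as meeting the rule. If data had to fall on days 0 to 14, about 85% would be lost (1 - 14/91). With earlier data accepted, the rule also admits patients it should exclude: 39.5/91 = 43% of those with a true lag of 20 days, and 29.5/91 = 32% at 30 days.

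**Person-time before time zero.** The mean of max(0, -e) is (45.5²/2)/91 = 11.375 days. As a share of the true first 90 days this is 11.375/90 = 12.6%, taken over all starters before any exclusion and ignoring deaths.

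**Grace period.** Mean overlap of the assigned with the true 90 days is (90 - 22.75)/90 = 75%; the minimum is (90 - 45.5)/90 = 49%.

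**Two-week windows.** A switch stays in its correct window only if e falls in one 14-day interval: 14/91 = 15.4%. About 85% of switches are misplaced.

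**HDF by day 90.** For a true HDF start on day s up to 90, the status is wrong if e > 90 - s, with probability (45.5 - (90 - s))/91 where that is positive:

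- s = 60: 15.5/91 = 17%
- s = 75: 30.5/91 = 34%
- s = 90: 45.5/91 = 50%

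The pattern mirrors beyond day 90, so only starts between about days 45 and 135 can be affected. Averaged over assumed switch times, the error is 12.6% (uniform over 0-90 or 0-180 days), 9.5% (exponential, mean 90 days) and 7.4% (exponential, mean 45 days). Patients who stay on one modality are not affected.

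**The case against.** The strongest reply is that the midpoint was never meant for these rules. The ♠ marker sits only on maximum follow-up and on 5-year survival, and the footnote draws a consequence only for length of follow-up. The exclusion carries a different marker. The subgroup with data at initiation and the session counts per two weeks presuppose day-level timing, which a masked calendar date permits if sessions are stored as days since initiation. In that case every error above is zero. The article is also a condensed account.

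This stands as a condition on the point, but does not remove it. The footnote assigns the midpoint as the initiation date without limiting its use, and the article mentions no relative-day variable. An analyst following the text could apply the midpoint throughout.

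Three further replies hold in part:

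- Under uniform starts, exclusion by position in the quarter is unrelated to prognosis or modality. By itself it costs sample size and does not bias the comparison.
- Both clones of a patient share one time zero, so the date error is not assigned by arm.
- The MSM uses neither the grace period nor the two-week windows. It does share the eligibility rule and the start of follow-up.

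A reader might also infer that assignment to HDF or HD would be mostly an artefact of the date rule. The calculation does not support that: HDF-by-day-90 status changes for a minority of switchers and for nobody who stays on one modality.

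**Conclusion.** The protocol contradicts itself on the resolution of its time origin. As written, quarter-level initiation with midpoint assignment cannot support the 14-day exclusion, the at-initiation subgroup, the two-week windows or the 90-day grace period.

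The size is conditional on the midpoint being day 0, exact session dates, uniform starts in a 91-day quarter and, for the first two figures, treatment from the true first day. On those terms, about 35% are wrongly excluded and 50% have sessions before time zero. About 13% of true first-90-day person-time falls before time zero, and about 85% of switches land in the wrong fortnight. HDF-by-day-90 status is wrong for about 7-13% of switchers, depending on assumed switch times.

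The article does not establish that these errors will occur. With days since initiation on file, the midpoint would affect only calendar placement and follow-up length. The choice must still be settled before analysis, because time zero decides who enters the cohort and which early deaths count towards the primary outcome. The 4 years 9 months figure is inconsistent in either case.

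**What to change.** State which date is day 0 for each rule, and do not use the quarter midpoint as time zero or for any 14-day, two-week or 90-day rule.

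- **If days since initiation are held:** use that variable for follow-up, eligibility, the subgroup, adherence and the grace period. Keep the 14-day exclusion. Restrict the midpoint to calendar placement.
- **If they are not held:** set time zero at the first recorded in-centre high-flux HD or HDF session and use the initiation quarter to confirm incidence. State that the 14-day exclusion and the at-initiation subgroup cannot be applied at day level. Add a sensitivity analysis limited to patients whose possible late entry is short, for example those with a first session early in the initiation quarter.

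In both cases, correct or explain the 4 years 9 months and bring it into line with the five-year survival and yearly hazard ratio estimands.

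The cost is protocol wording and a changed derivation, with no new data. The second route has a real downside: some patients may enter up to about a quarter after true initiation, having survived and possibly settled on a modality elsewhere. That late entry must be acknowledged as a limitation.

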### Treatment strategies

We will compare the initiation of HDF with the initiation of high-flux HD. Aligning study eligibility, treatment assignment, and the start of follow-up is essential to prevent immortal time bias. However, this alignment is challenging because many patients switch between HD and HDF over time, and patients often initiate incenter dialysis with HD and subsequently transition to HDF at a later stage, calling for an approach that can accommodate practice patterns and dynamic treatment strategies.

Therefore, we will implement two different methods of analysis. First, we will use the clone-censor weight (CCW) approach. This approach begins with the duplication each individual (creation of “clones”) at the start of follow-up (first dialysis initiation) and each clone will be assigned to either the HDF strategy or the HD strategy.

**HDF strategy:**

Initiate HDF within the first 90 days after dialysis initiation (grace period).Continue HDF throughout the grace period (receiving at least three HDF treatments every two weeks).

**HD strategy:**

Initiate HD within the first 90 days after dialysis initiation (grace period).Continue HD throughout the grace period (receiving more than three HD treatments every two weeks).

The 90-day grace period was selected based on the expectation that patients who transition to HDF generally do so within the first three months after dialysis initiation. Similarly, the definition of treatment continuation as receiving at least three HDF treatments every two weeks was based on clinical practice patterns. After assignment, clones are followed and censored in case they deviate from the assigned treatment strategy during the grace period of 90 days. In addition to this approach, we will use a Marginal Structural Model (MSM) to estimate the effect of sustained treatment with HDF versus sustained treatment with HD. For this model, follow-up will start at dialysis initiation, and treatment will be included as a time-varying covariate throughout the entire follow-up period.

Lastly, we will conduct additional analyses for both the CCW approach and MSM in which we will evaluate consistent treatment strategies, but with HDF redefined as achievement of high-volume HDF (≥ 23 L of convection volume). For the CCW approach, we will calculate the mean delivered convection volume for every two-week period within the grace period. For MSM, we will calculate the mean delivered convection volume for every six months.

### Interpretation and estimands

Both the CCW approach and MSM aim to estimate the average treatment effect (ATE) to quantify the causal effect of treatment strategies in the target population. However, the CCW approach compares the effect of initiating HDF within 90 days with not initiating HDF within 90 days, whereas the MSM compares the effect of sustained treatment with HDF versus sustained treatment with HD over the entire study period. In the CCW framework, treatment adherence is assessed during the predefined grace period, requiring full adherence to the assigned strategy within this window, irrespective of treatment changes thereafter.

### Outcomes

The primary outcome will be the cumulative incidence of all-cause mortality. Secondary outcomes will be cardiovascular mortality, infection-related mortality including COVID-19 and infection-related mortality excluding COVID-19. Additionally, all-cause hospitalization and cause-specific hospitalization, as well as the length of hospitalization (proportion of the follow-up time in days) will be analyzed. Standard International Classification of Diseases (ICD-10) codes will be used to determine these outcomes. ICD-10 codes that are used to determine the outcomes are summarized in Supplemental Table S2. Lastly, the dose-relationship between convection volume and outcomes will be investigated for patients receiving HDF, with convection volume analyzed as a continuous variable to preserve all information that would otherwise be lost through categorization.

### Statistical analysis

#### Sample size

No formal sample size calculation was performed, as all patients meeting the inclusion and exclusion criteria will be included in the study. We expect this sample size to be sufficiently large to answer the research questions, given the size of the Apollo database.

#### CCW approach

First, a stacked dataset will be created in which each individual is duplicated, creating one clone for each of the two treatment strategies. As a result, both treatment groups will be perfectly balanced at baseline. However, selection bias may arise after baseline because clones are followed over time and artificially censored when their observed data deviates from the assigned treatment strategy. Of course, patients can be censored both within the grace period and after the grace period due to competing risks, including kidney transplantation, recovery of kidney function or dialysis withdrawal. Both forms of censoring are likely to be informative. To address this issue, we will apply inverse-probability-of-censoring weighting (IPCW) using a generalized linear model (GLM) that includes covariates predictive of censoring and the outcome. We will determine weights for the grace period and the period thereafter separately. Weighting within the grace period will take place every two weeks, whereas weighting for the period after that will occur with yearly intervals. The probability of remaining uncensored will be the outcome of this model. To assess whether the weights adequately reduce covariate imbalance between the two arms due to artificial censoring during the grace period, we will calculate the standardized mean difference (SMD). A SMD above 10% will be considered evidence of residual imbalance, potentially indicating misspecification of the weight model [16]. The weighting approaches with the included covariates in each model of both CCW and MSM are summarized in Fig. 1.

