**Methods:**

Data will be obtained from the second version of ApolloDialDb (Apollo), an anonymized dialysis dataset capturing over 1000 variables from patients from all over the world. For this study, we will include adult patients from European countries with kidney failure who initiated with at least one treatment of high-flux hemodialysis or hemodiafiltration between 01 January 2018 and 30 June 2024, and who were prescribed a thrice-weekly dialysis schedule at the start. Patients starting with home dialysis will be excluded. We will use a target trial emulation approach with a clone-censor-weight design and marginal structural models, controlling for selection bias, survivor bias, and competing risk bias. Sub-analyses will be performed to investigate the effect of high-volume hemodiafiltration (≥ 23 L of convection volume). Inverse probability weighting will be applied to adjust for predefined confounders including sociodemographic, clinical, and anthropometric factors, as well as comorbidities to achieve balance between treatment groups.

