**Figure Fig6:**
[figure not shown]
Each two weeks in the first 90 days, adherence for the assigned treatment strategy is assessed. Data from all individuals are duplicates so there are two clones. Each clone is assigned to either the HDF strategy (orange) or the HD strategy (purple). ID, patient identifier; HDF, hemodiafiltration; HD, hemodialysis; wk, weeks

The outcome model will be a weighted pooled logistic regression model fitted over all time intervals on the stacked dataset to estimate the effect of the two treatment strategies. Country will be included as a random effect to account for clustering at the country level, reflecting differences in treatment practices and the varying likelihood of receiving treatment across countries. To account for the within-individual correlation introduced by cloning, 95% confidence intervals will be estimated using nonparametric bootstrap resampling at the individual level with 500 samples, ensuring that both clones of each resampled individual are retained within each bootstrap sample. Both weighted cumulative incidence curves, restricted mean survival time, as well as hazard ratios for each year during a total of five years will be used to illustrate the differential effect of the two treatment strategies on outcomes.

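### Transplantation, recovery of kidney function and dialysis withdrawal are called competing events but censored and weighted away, so the primary cumulative incidence of death is an undeclared hypothetical risk rather than the risk in routine practice

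*Protocol article*

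**What the plan says.** The Outcomes section of the protocol article sets the primary measure: "The primary outcome will be the cumulative incidence of all-cause mortality".

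Table 1 (Follow-up) ends observation at death, administrative censoring, loss to follow-up or "informative censoring due to a competing event (kidney transplantation, recovery of kidney function, withdrawal from dialysis"). The target-trial and emulation columns both do this, although the target-trial column is labelled intention-to-treat. The CCW approach section repeats that "patients can be censored both within the grace period and after the grace period due to competing risks, including kidney transplantation, recovery of kidney function". Its full list is "kidney transplantation, recovery of kidney function or dialysis withdrawal", so withdrawal is treated in the same way as the other two.

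Table 1 (Analysis plan) states that "IPCW is performed, both for informative and artificial censoring within the grace period, and for informative censoring after the grace period". For the estimate itself, the CCW section says: "The outcome model will be a weighted pooled logistic regression model fitted over all time intervals on the stacked dataset". The results are to be shown as "Both weighted cumulative incidence curves, restricted mean survival time, as well as hazard ratios for each year". The Marginal structural model section also applies IPCW for informative censoring, at 6-month intervals.

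Neither the Estimands row of Table 1 nor the section on interpretation and estimands says that the risk is conditional on these events being prevented. The latter section describes an average treatment effect in the target population, and the Background gives the aim as the effect in routine clinical practice.

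**The concern.** Censoring a competing event and reweighting for it answers a different question from the one that a cumulative incidence answers. When the weights are correct, patients who are transplanted, recover or withdraw are replaced by comparable patients who stay on dialysis. One minus the weighted survival is then the risk of death in a population where those three events never happen. A cumulative incidence in the presence of competing events lets them happen and counts only the deaths that occur first. IPCW deals with the dependence of the censoring on measured covariates, but it does not turn the first quantity into the second.

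The primary outcome is defined as an absolute risk. The curves, the risk difference read from them and the restricted mean survival time (RMST) are therefore all exposed. A reader told that the study describes routine practice would take them as mortality in a population where transplantation, recovery and withdrawal do occur. The weighted version also needs the predictors of each event to be measured. The Discussion says that functional status and echocardiographic cardiac function could not be included, and both plausibly bear on selection for transplantation.

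**Working it through.** The documents contain no event rate, sample size or power figure, so there is no figure of the plan's own to reproduce. The calculation shows how the size and direction depend on rates that have to be assumed.

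**Inputs.** The horizon is t = 4.75 years, from the Table 1 footnote on maximum follow-up (4 years and 9 months). Everything else is assumed: constant hazards of death (d), of transplantation plus recovery (c) and of withdrawal (w), death after transplantation or recovery at 0.03 per year (m), and a hazard ratio of 0.80 for HDF with no effect of HDF on c.

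**Formulas**

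- Plan's quantity: 1 − exp(−d·t)
- Competing-event cumulative incidence: d/(d+c) × [1 − exp(−(d+c)·t)]
- All deaths, including those after transplantation or recovery: 1 − exp(−(d+c)·t) − c/(d+c−m) × [exp(−m·t) − exp(−(d+c)·t)]

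**Step 1: transplantation and recovery only.** For d = 0.12 and c = 0.04:

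- Plan: 1 − exp(−0.57) = 43.4%
- Cumulative incidence: 0.75 × [1 − exp(−0.76)] = 39.9%
- All deaths: 1 − 0.468 − 0.308 × (0.867 − 0.468) = 40.9%

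Gaps in the table are taken from unrounded values, in points.

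| d | c | Plan | Cumulative incidence | Gap | All deaths | Gap |
|---|---|---|---|---|---|---|
| 0.08 | 0.01 | 31.6% | 30.9% | 0.7 | 31.2% | 0.4 |
| 0.12 | 0.04 | 43.4% | 39.9% | 3.5 | 40.9% | 2.5 |
| 0.16 | 0.04 | 53.2% | 49.1% | 4.2 | 50.0% | 3.2 |
| 0.20 | 0.08 | 61.3% | 52.5% | 8.8 | 54.3% | 7.1 |

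The first and last rows are the extremes of the grid d = 0.08 to 0.20, c = 0.01 to 0.08. If transplantation falls mainly on low-risk patients (40% with d = 0.05 and c = 0.08 or 0.12; 60% with d = 0.18 and c = 0.01), the plan gives 42.9% against a cumulative incidence of 40.9% or 40.3%, a gap of 2.0 to 2.6 points.

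**Step 2: add withdrawal.** The plan also censors withdrawal, so its figure stays at 43.4% for d = 0.12. Treat each withdrawal as a death at that time, which is an extreme assumption, by replacing d with d + w in the two comparison formulas. With c = 0.04:

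| w | All deaths | Plan minus all deaths | Cumulative incidence | Plan minus cumulative incidence |
|---|---|---|---|---|
| 0 | 40.9% | +2.5 | 39.9% | +3.5 |
| 0.01 | 43.4% | +0.1 | 42.4% | +1.1 |
| 0.02 | 45.7% | −2.2 | 44.7% | −1.3 |
| 0.04 | 50.0% | −6.6 | 49.1% | −5.6 |

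Over d = 0.12 to 0.16, c = 0.02 to 0.08 and w = 0 to 0.04, the difference from all deaths runs from +6.1 to −8.1 points.

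**Step 3: the contrast between arms, withdrawal set aside.** For d = 0.12 (HDF 0.096) and c = 0.04, the plan's risk difference is 43.4 − 36.6 = 6.8 points. The cumulative incidence difference is 39.9 − 33.6 = 6.3. Over d = 0.12 and 0.16 with c = 0.02 to 0.08, the shift is 0.26 (6.83 vs 6.57) to 0.96 (7.68 vs 6.72) points.

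**The case against.** Censoring with IPCW targets a recognised estimand, the effect of treatment with the competing events prevented, and a team may legitimately choose it. Death can also follow transplantation or recovery, so those events do not preclude all-cause mortality. Death before transplantation or recovery is therefore not the stated primary outcome either, and it would fall if HDF raised transplantation without changing the death hazard. The study's question is comparative, and the contrast moves little. The abstract's statement on "controlling for selection bias, survivor bias, and competing risk bias" can fairly be read as a promise to adjust for informative censoring, which the plan does.

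Most of this stands. It rules out calling the weighted analysis invalid, it argues against replacing that analysis outright, and little weight should be put on the abstract's phrase. It does not remove the mismatch: the estimand is never declared, and the name given to the primary outcome does not fit what is estimated.

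A reader might infer that the plan overstates routine-practice mortality, and by several points. The documents do not support that. They give no rates, and with c = 0.01 the gap is only 0.4 to 1.2 points. Withdrawal is censored in the same way, which leaves out the deaths that follow it and can offset or reverse the sign.

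**Conclusion.** The point holds as a mismatch between the named primary outcome and its estimator. With correct weights, the curve and RMST describe mortality and survival time with transplantation, recovery and withdrawal all prevented. The protocol does not say this, and it does not fit the routine-practice aim.

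For transplantation and recovery alone, the curve lies above the competing-event cumulative incidence, by 0.7 to 8.8 points under the assumed rates. No direction or size can be given for the whole curve, because withdrawal works the other way at a rate that is not stated. The risk difference shifts by about 0.3 to 1.0 points, assuming a hazard ratio of 0.80, constant hazards and no effect of HDF on the competing events. The hazard ratio is much less affected. The comparison of HDF with HD is therefore not undermined, but the absolute results need a declared estimand and a matching label before analysis.

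**What to change.** 1. State the estimand separately for transplantation, recovery of kidney function and dialysis withdrawal: whether each is allowed to occur or hypothetically prevented.
2. For both CCW and MSM, add a weighted Aalen-Johansen estimate, or a weighted discrete-time model for each event type, of the cumulative incidence of death before transplantation or recovery. Show the cumulative incidence of transplantation or recovery by arm beside it.
3. In that analysis, do not apply censoring weights to transplantation or recovery. Keep IPCW for artificial censoring, loss to follow-up and withdrawal, or define withdrawal explicitly as its own competing state. Dropping its weights without doing so would leave informative censoring unaddressed. If withdrawal stays weighted, the label must say that the risk assumes no withdrawal.
4. Keep the present IPCW curve and RMST, labelled as the risk and survival time had these events not occurred, and do not describe them as cumulative incidence in routine practice.

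The cost is some wording and one extra event-type model, using events that the plan already records as reasons for censoring. No new data are needed. The downside is that any arm difference in transplantation has to be read together with the death curve.
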